### Reducing contamination

Contamination may occur when people from one cluster have contact with people from another. In the rural villages of Mchinji, there are many opportunities for social mixing. Friends, relatives or neighbours may mix socially, or contact may be made through travel or migration between intervention and control clusters. There might be direct participation of residents from control areas in WG or VMC activities, or more likely, informal discussion of ideas from WG or VMC activities - control area residents may gain some benefit from hearing health messages received by intervention participants. The usual effect of this kind of contamination would be 'dilution' of the differences between treatment arms [43].

In order to reduce the possibility of contamination, we opted to use clusters of villages rather than individual villages as the unit of randomisation, thus reducing rates of travel across cluster boundaries [43]. Furthermore, each zone had a defined 'buffer area' around the perimeter (figure 2). A population of 3000 in each zone was required to achieve the desired sample size, but rather than selecting villages at random from each zone, only villages at the centre of the zonal area were eligible for inclusion in surveillance and intervention activities. This reduced the possibility of communication between neighbouring study villages in intervention and control areas.

Women's group facilitators and volunteer counsellors are residents of the zone in which they work. This reduces the possibility that they might transfer intervention benefits to neighbouring communities. For the WG trial, whilst health messages are discussed in group meetings, it is unlikely that neighbouring control communities would spontaneously mobilise themselves without the presence of a facilitator. So the purported benefits of community empowerment and social capital are unlikely to spread beyond intervention areas.

### Interim analyses and stopping rules

An independent Data Safety and Monitoring Board (DSMB) will meet several times according to the DAMOCLES statement, [44] to review progress and advise on the conduct of the trial. They will assess compliance with the protocol, data quality and completeness, recruitment figures, sample size assumptions and ethical considerations. The meetings will not include analysis of outcome data by intervention allocation until completion of the trial. Baseline data will be reviewed to evaluate how well balanced the clusters were after randomisation and suggest any adjustments that may need to be made. We do not foresee any adverse effects of community mobilisation or peer counselling, so we do not intend to apply stopping rules.

### Analysis plan

Data from the trial will be analysed by intention to treat at both cluster and participant levels. Participants will be assigned to the cluster they were resident in at the time the trial began, even if they move to another cluster or out of the study area during the trial period. Primary and secondary outcomes will be compared between intervention and control groups with random effects logistic regression models, taking account of clustering. Potential confounding factors will be included in the model, and measures of baseline mortality will be included in order to adjust for any imbalances in randomisation at the outset. Cluster-level data will be compared using modified t-tests. All estimates will be presented with 95% confidence intervals.

Data collected from the project both during the baseline phase and the intervention phase mean that we will be able to look at overall changes in outcome indicators over time. Factors other than the study interventions may influence health indicators seen, such as other mother and child health programs in the area, or positive reporting and the Hawthorne effect [45]. If mother and child health programs are only active within some of the cluster areas then these can be examined separately if necessary.

Analysis of qualitative data will involve iteratively developing a system of codes and memos jointly by the lead researcher and the researcher who collected the data. This method will seek to develop an analytical framework based on the data by coding and memoing pertinent excerpts that illustrate emerging themes. Subsequently, in an iterative process, the researchers will refine their analysis ensuring that the themes that are built up are cross-checked with other data firstly within and then between transcripts so that the validity of emerging explanations is tested and improved. The qualitative data will also be used to interpret and contextualise the quantitative data collected. MAXqda 2 software will be used to facilitate this analysis.

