## Methods/Design

### Study design

The intervention will be evaluated in a cluster-randomised controlled trial. A cluster design has been chosen because the allocation and loci of delivery of the interventions (community clusters) are groups rather than individuals. 48 rural clusters have been identified. 24 have been allocated to receive the women's group intervention and 24 will act as controls. Using a factorial design, each of these arms of the women's group trial was randomized a second time, 12 clusters to receive the volunteer counseling intervention and 12 to act as controls. An independent surveillance system for outcomes - births, morbidity, mortality, and care seeking - has been designed and implemented in all 48 clusters, covering a population of 144,000 (Figure 1).

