### Design and unit of randomisation

A cluster-randomised controlled trial, with a two-by-two factorial design, will be used to test the impact of two interventions on specific outcome indicators. 48 clusters or 'zones' were defined from the Enumeration Areas generated during the 1998 census (Figure 2a). Each zone contained a population of approximately 8000 in total. A population of around 3000 was selected from the centre of each zone, leaving a 'buffer area' around it to reduce contamination between neighbouring intervention and control areas (Figure 3).

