### Randomisation and allocation

The 48 study zones were randomly allocated to one of four groups; 12 zones receiving infant feeding counselling and facilitation, 12 zones receiving facilitation only, 12 zones receiving infant feeding counselling and no facilitation, and 12 zones receiving neither (Figure 1 and Figure 2b). All zones will benefit from the district-wide training and support for health services from the project's initiation.

Random number generation was done in STATA 7.0, and each of the 48 clusters was allocated to one of four possible combinations of interventions. In this way, each intervention was stratified according to the presence or absence of the other one, in order to balance any effects of one intervention on outcomes of interest in the other. SL and DO generated the random number sequence and allocated the clusters to intervention groups. All women aged between 10 and 49 years residing within the clusters were eligible for inclusion in the interventions and follow-up of maternal and child health outcomes. Records of a woman's migrations within and outside of the study area are recorded in order to allow for both 'intention to treat' and 'per protocol' analysis.

Due to the nature of the interventions, blinding of study participants to their allocation was not possible, though analysts and trial monitors will be blinded to the study allocation until the definitive analysis is performed. Data will be collected independently from intervention implementation, and no results will be fed back to inform the interventions.

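### Each intervention was allocated in strata of the other, but the analysis as described does not carry the other allocation into the main-effect comparisons, which would cost precision if it were left out

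*Protocol article*

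**What the plan says.** The design is a balanced factorial: "A cluster-randomised controlled trial, with a two-by-two factorial design, will be used to test the impact of two interventions on specific outcome indicators". Under Study design, "24 have been allocated to receive the women's group intervention and 24 will act as controls". Both sets of clusters were then divided at random, half with counselling and half without. Randomisation and allocation gives the reason: "each intervention was stratified according to the presence or absence of the other one, in order to balance any effects of one intervention on outcomes". The outcomes meant there are those of the other intervention. The authors therefore expected that one intervention might move the other's outcomes.

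The Analysis plan describes two analyses. At participant level, "Primary and secondary outcomes will be compared between intervention and control groups with random effects logistic regression models, taking account of clustering". On covariates, "Potential confounding factors will be included in the model, and measures of baseline mortality will be included in order to adjust for any imbalances"; the imbalances meant are chance differences between the arms at the start. At cluster level, "Cluster-level data will be compared using modified t-tests"; how the test is modified is not stated. Neither description names the other intervention as a model term or a stratum.

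Table 1 makes infant mortality a primary outcome of both interventions. Exclusive breastfeeding (EBF) is primary for counselling and secondary for women's groups. The section on interactions between the two interventions plans to explore synergy, and says the trial is not powered to compare the combination with single interventions on mortality.

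**The concern.** In a main-effect comparison of 24 with 24 clusters, each arm contains 12 clusters with the other intervention and 12 without. Balance keeps the other intervention from biasing the contrast. It does not keep that intervention's effect out of the error term: unless the analysis recognises the strata, the gap between the two halves of each arm is counted as ordinary cluster-to-cluster variation.

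The allocation removes this source of variation from the estimate, so an analysis that leaves it in the standard error overstates the uncertainty. Precision that the design has already paid for is lost. This matters most where both interventions act on the same outcome, above all infant mortality.

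**Working it through.** **Inputs.** From Table 5 and the sample size text: 48 clusters, 252 births per cluster, k from 0.15 to 0.30, two-sided 5%, 80% power, infant mortality 76 per 1000, EBF 27.5%. The effect of the other intervention is not given for this purpose. It is assumed equal to the Table 5 detectable value that belongs to the same k.

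**Step 1: reproduce Table 5.** Clusters per arm:

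c = 1 + (1.96 + 0.84)² × [V + k²(p0² + p1²)] / (p0 − p1)²

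Here V = (p0 + p1)/n for mortality and [p0(1 − p0) + p1(1 − p1)]/n for EBF. The squared factor, unrounded, is 7.849.

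- Infant mortality, 21% reduction, k = 0.15: p1 = 0.06004, V = 0.000540, k² term = 0.000211, squared difference = 0.000255, so c = 24.1.
- Infant mortality, 28% reduction, k = 0.30: p1 = 0.05472, V = 0.000519, k² term = 0.000789, squared difference = 0.000453, so c = 23.7.

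Solved with c = 24, the formula gives 21.1–27.8% for infant, 31.0–35.5% for neonatal and 47.0–49.6% for maternal mortality, and 16.0–30.1% for EBF. These match Table 5. With 12 clusters per arm infant mortality would be 29.6–38.6%, which does not match. The stated power therefore rests on the 24-versus-24 main-effect comparisons.

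**Step 2: variation added by an ignored factor.** If the other intervention changes the rate by a proportion r in half the clusters of each arm, the arm mean is multiplied by (1 − r/2) and the added coefficient of variation is (r/2)/(1 − r/2).

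- r = 0.21: 0.105/0.895 = 0.117. Effective k = √(0.15² + 0.117²) = 0.190.
- r = 0.28: 0.14/0.86 = 0.163. Effective k = √(0.30² + 0.163²) = 0.341.

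**Step 3: interval width and power, infant mortality.** The control-arm rate becomes 76 × 0.895 = 68.0 or 76 × 0.86 = 65.4 per 1000.

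- k = 0.15, r = 0.21: variance sum 0.000756 with the factor omitted, 0.000652 with it included. Width ratio = √1.159 = 1.08.
- k = 0.30, r = 0.28: 0.001202 against 0.001030. Width ratio = √1.167 = 1.08.

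At an effect that has 80% power with the factor included, power with it omitted is Φ(2.80/1.08 − 1.96), about 74% in both cases: a loss of about 6 points.

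**Step 4: simulation.** 20,000 trials per row, 12 clusters per cell, 252 births per cluster (Monte Carlo error about 0.3 points). A two-sample t-test on cluster rates (46 df) is compared with the same contrast adjusted for the other factor (45 df).

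| Outcome | k | Effect tested / other effect | Width ratio | Power, omitted | Power, included |
|---|---|---|---|---|---|
| Infant | 0.15 | −21% / −21% | 1.08 | 73.4% | 78.6% |
| Infant | 0.30 | −28% / −28% | 1.08 | 73.8% | 78.9% |
| Neonatal | 0.15 | −31% / −31% | 1.07 | 70.0% | 75.0% |
| Neonatal | 0.30 | −36% / −36% | 1.08 | 71.5% | 76.4% |
| Maternal | 0.15 | −47% / −21% | 1.01 | 75.8% | 76.4% |
| Maternal | 0.30 | −47% / −21% | 1.01 | 71.7% | 72.4% |
| Infant | 0.15 | −21% / none | 1.00 | 82.1% | 82.1% |

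In the first row the mean estimated difference is −0.0143, and the expected value is 0.076 × 0.895 × (−0.21) = −0.0143, so there is no bias. The true standard deviation of the estimate is 0.00507. The average standard error is 0.00549 with the factor omitted and 0.00508 with it included. When the tested intervention has no effect and the other cuts infant mortality by 28% (k = 0.30), the unadjusted test rejects 3.3% of the time, not 5%.

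**Step 5: EBF as a women's group outcome.** For an increase the added coefficient of variation is (r/2)/(1 + r/2).

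- k = 0.15, r = 0.16: 0.08/1.08 = 0.074, effective k = 0.167. The detectable relative increase moves from 15.7% to 17.1%.
- k = 0.30, r = 0.30: 0.15/1.15 = 0.130, effective k = 0.327. It moves from 29.8% to 32.7%.

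**The case against.** The strongest reply is that silence is not exclusion. The covariate list is open-ended, the modification of the t-test is undefined and could be stratification, and a quantitative look at synergy needs both allocations in one model. This is a journal article, and a separate analysis plan may hold the full model.

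Much of this stands. A reader might infer that the protocol excludes the other allocation or prescribes an unstratified t-test. It says neither, and that reading is not supported.

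The reply does not dispose of the point. The article does describe the main-effect analysis and what enters it. A factor balanced by design is not a confounder, and the stated purpose of the baseline adjustment is to correct imbalance, so the description gives no reason to include this factor. The synergy analysis is exploratory and does not set the main-effect model. The stratification stated for the allocation is thus not carried into the analysis as described.

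It is also fair to say that the harm is modest: no bias, no excess of false positives, and no loss if the other intervention does nothing.

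**Conclusion.** The point holds as a gap between the stated allocation and the stated analysis, with loss of precision as the consequence if the other factor is left out. For infant mortality at matched Table 5 values, intervals would be about 8% wider and power about 5 to 6 points lower. Neonatal mortality behaves similarly if both interventions reduce it. For EBF in the women's group comparison, the detectable relative increase moves from about 16% to 17%, or from about 30% to 33%. For maternal mortality the loss is under 1 point if counselling reduces it by 21%; it is not a listed outcome of counselling.

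The size depends on the assumed effect of the other intervention. Larger figures come from less natural pairings. A 28% reduction combined with k = 0.15 brings power down to 69%, but Table 5 ties 28% to k = 0.30. A doubling of the detectable EBF increase, from 15% to 32%, needs counselling to lift EBF from 27.5% to 50%, an 82% relative rise against the 16–30% in Table 5. Neither should be taken as the expected loss.

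The calculations are for the cluster-level comparison. In the random effects logistic model the same mechanism applies, since an omitted cluster-level factor is absorbed by the random intercept, but its size was not computed separately.

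**What to change.** Add to the Analysis plan: for every primary and secondary outcome, the main-effect model for one intervention includes the other intervention's allocation as a fixed effect, and the cluster-level t-test is stratified by that allocation (48 − 3 = 45 degrees of freedom). Keep the exploration of synergy as a separate analysis. If a full analysis plan already specifies this, the article need only say so.

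The cost is one sentence, one model term and one degree of freedom; the two-sided 5% critical value stays at about 2.01. Nothing changes in the allocation, the sample size or the data collected.

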### Ethical issues

#### Approvals

Ethical permission for this study was granted by the Malawi National Health Sciences Research Committee in January 2003 (Ref: MED/4/36/I/167) and the ethics committee of the UCL Institute of Child Health and Great Ormond Street Hospital. It is registered with ISRCTN06477126.

#### Community consultation

Verbal and written consent was received from community leaders after full consultation and discussions. The regional, district and village leaders, and local health and development professionals will have ongoing access to the research programme and will be the first to be briefed on study findings and outcomes through written and verbal reports.

#### Individual consent

Before each instance of data collection, the process and advantages and disadvantages of taking part will be explained to all participants. Verbal consent will be obtained, and participants informed that they can stop taking part at any time. Participation in intervention activities is voluntary, and women may choose to start or stop as they wish.

#### Benefits to the control communities

The study is designed to test the community effectiveness of two community-level initiatives to reduce maternal, infant, neonatal and perinatal mortality in rural Africa. Encouraging community action for maternal and newborn care alone will not grant success. For health promotion interventions to work, the supply side of health care services must reach a minimum standard. The study team considers it unethical to strengthen services only in intervention and not control areas. Control communities will benefit from low-cost improvements in equipment, supplies and training at all primary level facilities in the district in intervention and control areas.

#### Treatment of illness in participating communities

When the study workers identify minor or chronic illness in mothers or infants in either intervention or control areas they will encourage referral to the appropriate health facility.

#### Confidentiality of information

All information will remain confidential. Access to information will be limited to interviewers and their supervisors at sites of collection, to auditors and data feeders at the collation point and thence to the senior data management officers and principal investigators. No analyses or reports will include the names of participants.

### Sustainability and scalability

A key objective is to take lessons learned quickly to scale in other districts, through our partners. The Ministry of Health in Malawi will be involved throughout the implementation of this project. At a local level we will work closely with the district development committees, local community representatives and locally active NGOs. The Mchinji District Health Office will play a key collaborative role. We will also work closely with UNICEF, Malawi and the National AIDS Commission, to implement PMTCT activities.

Community-based team members have been recruited locally and carry out their activities in their home areas. We will attempt to maintain intervention costs to a minimum so that they can be adopted by the Ministry of Health.

Control areas will be the first beneficiaries of scale-up if either of the interventions prove to have a positive impact.
